### The ‘E-health4Uth Healthy Toddler’ intervention

The ‘E-health4Uth Healthy Toddler’ intervention provides tailored health education for the parents regarding the key behaviors related to childhood overweight prevention, at child age 18 and 24 months. These key behaviors are: (1) Promotion of daily exercise and outdoor playing, (2) Promotion of having breakfast daily, (3) Discouragement of drinking sweet drinks, and (4) Discouragement of TV viewing and computer use, including discouragement of playing computer games [7]. One month prior to the regular YHC visit at child age 18 months, parents receive an invitation to visit the ‘E-health4Uth Healthy Toddler’ website to obtain tailored parenting and health information prior to the YHC-visit, which can be used by the parents to prepare for the face-to-face visit at the YHC office (Table 3). During the counseling session, parents and the YHC professional discuss any issues that arose from the tailored feedback; the YHC professional, with permission of the parents, also has access to the results of the ‘E-health4Uth’ online assessment and tailored information. Approximately one month after the face-to-face counseling, the parents receive a reminder by email including the tailored advice. At child age 24 months, i.e. approximately one month prior to the next regular visit to the YHC center, parents allocated to this intervention group again receive an invitation to visit the ‘E-health4Uth Healthy toddler’ website to obtain tailored information prior to the YHC-visit (Table 3). This feedback again is discussed during the YHC-visit. Circa one month after the second face-to-face counseling, parents receive a reminder by email including the tailored advice.

**Table 3 T3:** Schematic overview of the ‘E-health4Uth Healthy Toddler’ intervention

**Steps according persuasion-**	**Element of the ‘Healthy**		**Age of the**
**communication model [**[20]**]**	**Toddler’ intervention**	**Content/activities**	**child**
Attention for the health message	1^st^ E-health module	- Assessment of four key behaviors	± 18 months
		- Assessment of parenting behavior	
		- Feedback on four key behaviors, in comparison with recommendations	
		- Tailored advice, taking into account the four behaviors and parenting practices	
Changing determinants and behavior:	Counseling with motivational interviewing technique	- Making parents aware of their child’s behavior	± 18 months
		- Motivate parents to prevent overweight in their child	
- Attitude			
- Self-efficacy		- Stress the parents responsibility and importance of strict parenting	
- Parenting behavior		- Motivate parents to change their parenting	
		- Discuss advantages of strict parenting	
		- Discuss potential barriers (e.g. time constraints)	
		- Improve self-efficacy	
		- Provide parenting skills:	
		- Setting rules, giving good examples, use praise and award, do not use food as a means of control	
Maintain behavior change	Reminder	- Reminder of tailored advice from E-Health module	± 18 months
		- Positive feedback	
	2^nd^ E-health module	- Assessment of four key behaviors	± 24 months
		- Assessment of parenting behavior	
		- If behavior change was achieved, parents receive positive feedback. If not, parents receive tailored advice	
	2^nd^ Counseling with motivational interviewing technique	- Assessment of behavior	± 24 months
		- If behavior is improved, provide positive feedback. If not, repeat activities described in 1^st^ counseling	
	2^nd^ Reminder	- Reminder of tailored advice from E-Health module	± 24 months

The intervention is based on the social-ecological model [15], which recognizes the importance of environmental and personal factors on health behavior. In very young children, parents can be considered as the main mediators of the toddler’s environment. According to this model, parents influence the social and physical environment through their general parenting style [16] and parental practices. Fostering an ‘authoritative’ parenting style has shown to decrease food stimuli at home [17]. Therefore, parenting is addressed in order to change the toddler’s behavior. Important determinants of parental behavior can be found in classical behavior change theories, such as the Theory of Planned Behavior [18] and Social Cognitive Models [19]. These theories include attitude, social support, self-efficacy, perceived barriers, knowledge, and awareness. The ‘E-health4Uth Healthy toddler’ intervention aims to create parental awareness of potential future overweight related problems, and motivate parents to prevent the development of overweight in their children from early age on by improving the four key behaviors defined in the YHC-Overweight Prevention Protocol. Positive attitudes of the parents towards applying strict behavior and positive attitudes towards the specific, recommended, parental practices are promoted. Furthermore, parents are supported to overcome barriers for not applying these practices, and the intervention promotes specific skills in order to be able to change their parenting according to the recommendations of the YHC-Overweight Prevention Protocol [7].

According suggestions proposed by McGuire for successful communication, several steps are required in order to achieve behavior change [20]. First, the prevention of potential/future overweight related problems have to be brought to attention and made understood. Second, determinants of the behavior have to be changed (e.g. create a positive attitude towards the recommended behavior, and increase self-efficacy to perform the behavior). Finally, behavior change has to be maintained using feedback and reinforcement. The ‘Healthy toddler’ intervention package follows this scheme by application of the different elements included in this intervention package (see Table 3).

At the child age 18 months, the E-health module is introduced to the parents along with the regular invitation for the scheduled YHC visit. This brings the topic to the attention of parents, prior to visiting the YHC center. Results from a pilot study with the ‘E-health4Uth Healthy Toddler’ showed that the majority of the parents indeed understand the message and view this message as useful and applicable. During the subsequent face-to-face counseling at the YHC center, the YHC professional increases knowledge, awareness, and addresses attitudes and self-efficacy with regard to relevant parenting practices. The YHC professionals apply motivational interviewing, which has proven to be effective in changing health behaviors in various settings and which has been adapted for this specific YHC application [21]. Finally, approximately one month after the face-to-face counseling at the YHC center, parents receive an electronic reminder regarding their tailored advice, also including this tailored advice. The intervention is repeated at the child age 24 months.

The ‘E-health4Uth Healthy Toddler’ intervention is delivered to the parents through an Internet-based E-health module. This module has the potential of reaching almost all parents, as 94% of the Dutch households have Internet access [22]. This E-health module assesses the four priority behaviors defined by the YHC-Overweight Prevention Protocol, the general attitudes of the parents toward overweight prevention from early age on, and whether parents apply the recommended parental practices. Participants receive feedback tailored to their individual situation given the provided answers posed by the E-health module online. As part of the tailored feedback, current behavior is compared to the recommendations for each of the four key behaviors. This promotes awareness of the parents regarding their behaviors.

Additionally, parents receive tailored advice on how to change their child’s behavior (e.g., setting rules) [7]. The information entered by the parents regarding the four key behaviors and a summary of their attitudes generated by the E-health module is also available to the YHC professional prior to the visit, enabling the professional to use this information in the counseling session.

YHC professionals in the ‘E-health4Uth Healthy Toddler’ intervention groups are trained to use the intervention and to apply motivational interviewing [23] in the context of the YHC overweight prevention protocol during a half-day session prior to the start of the intervention. This training is given by a certified trainer in motivational interviewing techniques, as applied in preventive health care. Training is performed in groups of 10–25 YHC professionals. The following elements are included in the training: (1) Stimulation for making parents aware of the risk for overweight and its potential adverse effect for their child, (2) Stimulation for favorable change of parental attitudes and motivations regarding overweight prevention and authoritative parenting, (3) Stimulation for the parent’s perception of being responsible for the health of their child, (4) Stimulation for goal setting and providing feedback regarding realistic goals that may increase authoritative parenting and improve energy balance-related behaviors in their child, (5) Providing information on beneficial parental practices and stimulating to teach parents these skills, and (6) Providing information on useful sources of information for parents.

### The control condition: care as usual

The control condition consists of parents of preschool children that participate in the study and receive preventive Youth Health Care from one of the YHC teams that apply ‘usual care’ (i.e., control condition). Usual care includes the regular scheme of YHC visits. The YHC professionals in the control condition are aware of the principles of the Overweight Prevention Protocol; i.e. the importance of healthy lifestyles for the prevention of overweight and obesity (promotion of breast feeding, daily exercise and outdoor playing time, having breakfast daily, lessening sweet drinks, and limiting TV time during their contacts with parents and children) [2,7]. However, in the control condition the YHC professionals did not receive any specific training regarding overweight prevention (as was provided in the ‘BBOFT+’ condition and in the ‘E-health4Uth Healthy Toddler’ condition), no specific supporting materials were available such as a calendar-like booklet on the desk of the professional with pictures to support counseling (as was available in the ‘BBOFT+’ condition), and no E-health support was available for parents (as was provided to parents in the ‘E-health4Uth Healthy Toddler’ condition).

### Measurements

Height and weight are measured at each YHC visit using standardized protocols [6], including height and weight at the visit at age 36 months; these data are collected from the YHC files. Parents are invited to complete questionnaires about overweight-related behaviors and determinants of these behaviors, and regarding health-related quality of life [24]. The questionnaires are provided to parents at inclusion (child circa 2 to 4 weeks old), and at child age 6, 13 and 36 months. YHC-professionals are invited to complete a brief questionnaire to gather information about their experiences regarding the care provided to the parents/children and regarding the specific intervention; this was done three times in the ‘BBOFT+’ and in the control group, and two times in the E-health4Uth group. Professionals in the ‘E-health4Uth Healthy Toddler’ intervention group are invited to complete a brief assessment form after the YHC-visit at age 18 and 24 months (i.e., process information and perceptions regarding the care).

The outcomes are measured at age 3 years; the measurements at inclusion, at child age 6 and 13 months can additionally be taken into account in the evaluation of the interventions. The primary outcome measures of the study are: (1) overweight inducing/reducing behaviors (i.e. activity and outdoor play, breakfast, drinking sweet beverages and watching television and devoting time to the computer and playing computer games; the ‘BBOFT+’ intervention also has a more healthy sleeping pattern as outcome; (2) Body Mass Index (BMI) and the prevalence of overweight and obesity. Children are categorized as overweight and obese based on internationally accepted gender and age-specific cut-off values for BMI [25].

Concerning the primary outcomes it is hypothesized that more favorable energy balance related behaviors (and a more healthy sleep pattern with regard to ‘BBOFT+’), a lower BMI and a lower proportion of children with overweight and obesity will be present in each intervention group, compared to the control group.

Secondary outcome measures are attitudes and other cognitive determinants of the parents regarding the health behaviors of their child, parenting styles and practices, and child health-related quality of life: (1) Attitudes, motivation and perceived control among parents regarding the four energy balance-related behaviors [24], (2) General parenting styles and parental practices and rules (these will be measured by Child rearing questionnaire for parents [26] and parenting practices and rules in relation to physical activity and food [27]), (3) Child health-related quality of life and wellbeing (Infant Toddler Quality of Life questionnaire - ITQOL) [24]). Concerning the secondary outcomes it is hypothesized that more favorable attitudes and other determinants of the parents regarding the overweight-related behaviors of their child will be present in each intervention group, compared to the control group. It is hypothesized that general parenting styles are less often restrictive and permissive, and more often authoritative in each intervention group compared to the control group, and that parenting practices and rules in relation to physical activity and food are more favorable in each intervention group, compared to the control group. It is hypothesized that child health-related quality of life and well-being are more favorable in each intervention group, compared to the control group.

We will explore whether one or more of the following variables have an effect on the relationship of interest, and if so, include them in the analyses as confounder: (1) Pregnancy duration and birth weight (from YHC files), (2) Parents’ BMI using self-report (self-report of adult height and weight has proven to be sufficiently accurate for epidemiological research [28]), (3) Parents’ health-related quality of life and wellbeing (SF-12), (4) Age, educational level and ethnic background of the parents.

In both intervention groups (i.e., ‘BBOFT+’ and the ‘E-health4Uth Healthy Toddler’) characteristics of the care process are measured via the questionnaires for parents at child age 6, 13 and 36 months [29]. YHC-professionals are invited to complete a brief questionnaire to gather information about their experiences regarding the care provided to the parents/children and regarding the specific intervention; this was done three times in the ‘BBOFT+’ and in the control group, and two times in the ‘E-health4Uth Healthy Toddler’ group. The questionnaires include: (1) Adherence of YHC professionals to the distinct elements of the intervention, (2) Appreciation/satisfaction of the interventions [29], and (3) Description of additional time investment. Professionals in the E-health4Uth Healthy Toddler intervention group are invited to complete a brief assessment form after the YHC-visit at age 18 and 24 months (i.e. care provided and perceptions regarding the care).

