**Figure 1 F1:**
[figure not shown]
Flowchart of the design of the study.

Managers of all regional Youth Health Care (YHC) organizations in the Netherlands (n=50) were informed about the study and were invited to participate in the study. Ten YHC organizations volunteered to participate. In total, 51 YHC teams were available to participate in the study (three times seventeen teams). These teams covered both rural and urban regions in the Netherlands. Prior to the start of the study, the researchers arranged meetings to explain the procedure of the study, and to instruct the participating YHC professionals. Within each organization, YHC teams were randomly assigned to either one of the two intervention groups or the control group by a computerized random allocation generator. Data collection started in 2008 and continues until fall 2013.

The Medical Ethical Committee of Erasmus Medical Center has declared that the Medical research Involving Human Subjects Act (also known by the Dutch acronym WMO) does not apply to this study. The Medical Ethical Committee had no objection against the execution of this research proposal (reference number MEC-2008-250).

The study includes parents and their babies/toddlers that belong to one of the participating YHC teams, and who are eligible for the regular YHC visits from birth until age three years. The parents are informed about the study when the YHC nurse visits the parents in the second week after birth. Parents are provided with information about the study, an informed consent form, and a short questionnaire with items on background data (i.e. the baseline questionnaire); the parents were invited to provide written informed consent to participate in the study, and to complete the short questionnaire. The study design and participant flow are shown in Figure 1.

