### Data analyses

To assess the effect of both interventions, multilevel analyses will be applied to allow for dependency between the individual measurements within the YHC teams [30]. Multilevel linear and logistic regression analyses will be conducted for the continuous outcome variables with experimental group (i.e., intervention or control) as independent variable, and baseline values and relevant potential confounders, if any, as covariates. Multilevel logistic regression will be performed for dichotomous outcome variables. Additionally, by introducing an interaction term into the regression analyses, effect modification by gender, parental educational level, parent ethnic background, and parental overweight status will be explored. If any of these interaction terms reach statistical significance, stratified analyses will be performed.

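### Covariates enter the primary models only if they are seen to alter the intervention effect; a set named in advance for each outcome would remove that discretion and recover some precision

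*Protocol article*

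**What the plan says.** The article's Measurements section gives a closed list of candidates: gestational length and birth weight, the parents' self-reported BMI, the parents' SF-12, and parental age, education and ethnicity. Their entry is conditional: "We will explore whether one or more of the following variables have an effect on the relationship of interest, and if so, include them". Those that pass are treated as confounders ("include them in the analyses as confounder"). No threshold or procedure is stated.

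The Data analyses section gives the covariates of the multilevel models as "baseline values and relevant potential confounders, if any, as covariates". Baseline values are therefore unconditional and the rest are not. Effect modification is handled separately there, through interaction terms that include gender. The Measurements rule is therefore most naturally read as a check for confounding by change in estimate.

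Allocation was random at team level: "YHC teams were randomly assigned to either one of the two intervention groups or the control group by a computerized random allocation generator". On recruitment, the Study design section says: "The parents are informed about the study when the YHC nurse visits the parents in the second week after birth".

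**The concern.** Screening covariates by their influence on the exposure-outcome association is a habit from observational work. In a randomised comparison, the reason to adjust is mainly that a covariate predicts the outcome, and that can be judged beforehand. Under the stated rule:

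- The observed effect helps to decide which model is reported. There are several primary outcomes (behaviours, sleep for BBOFT+, BMI, overweight and obesity) and two comparisons with control, so the covariate set can differ for each.
- A strong predictor that happens to be balanced moves the estimate little, so it may be left out, although including it would narrow the interval.
- For the logistic models the rule does not isolate confounding. Odds ratios are non-collapsible, so a prognostic covariate shifts the estimate even when it is perfectly balanced.
- For BMI as a continuous outcome at about 36 months, child sex and exact age at measurement are not candidates. Sex appears only as an exploratory effect modifier.

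At stake are the credibility of the primary estimates as planned analyses, and some precision.

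**Working it through.** **The plan's own figure.** Inputs from the Size of the study section: 1250 children with complete data over three groups (3570 × 0.5 × 0.7 = 1249.5), cluster size 25, ICC 0.10, two-sided 0.05, power 0.80, BMI SD 1.3.

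Design effect = 1 + 24 × 0.10 = 3.4. Detectable difference = SD × (1.960 + 0.842) × √(2 × 3.4 / n).

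- n = 1250/3 ≈ 417 per arm: 0.465, not the stated 0.38.
- n = 1250/2 = 625 per arm: 0.380.

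So 0.38 is not reproduced with the stated three-way split. That is a separate matter. It is relevant here only because power at 0.38 with 417 per arm is about 0.63, which leaves little precision to spare.

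**What fixed covariates could add.** The article gives no explained variance (R²), so a range is assumed. The residual SD, and with it the standard error, scales by √(1 − R²):

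| R² | SE reduction against no adjustment | BMI detectable difference, 417 per arm | Power at 0.38 |
|---|---|---|---|
| 0 | 0% | 0.465 | 0.63 |
| 0.05 | 2.5% | 0.453 | 0.65 |
| 0.10 | 5.1% | 0.441 | 0.67 |
| 0.15 | 7.8% | 0.429 | 0.70 |
| 0.20 | 10.6% | 0.416 | 0.73 |
| 0.30 | 16.3% | 0.389 | 0.78 |

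Screening already captures part of this, so the gain of a fixed set over screening is smaller than the second column and vanishes as R² falls to zero.

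**Screening against a fixed set.** Simulation of one comparison: 17 against 17 teams of 25 children, ICC 0.10, 4000 runs per scenario, outcome in SD units. Assumed: 8 candidates with joint R² 0.17, covariate ICC 0.05 or 0.15, and a 10% change-in-estimate criterion. Check: the theoretical unadjusted SE is √(2 × 3.4 / 425) = 0.126, and the simulation gave 0.126 to 0.127.

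| True effect 0.29 SD | Unadjusted | Screened | Fixed set |
|---|---|---|---|
| Mean SE, covariate ICC 0.05 | 0.1270 | 0.1238 | 0.1158 |
| Mean SE, covariate ICC 0.15 | 0.1261 | 0.1220 | 0.1162 |
| Power (ICC 0.05; 0.15) | 0.61; 0.60 | 0.64; 0.64 | 0.69; 0.68 |

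Fixed against screened: 1 − 0.1158/0.1238 = 6%, and 1 − 0.1162/0.1220 = 5%. A second simulation (3000 runs, covariate ICC 0.10, residual team variance 0.08, similar R²) gave 0.124, 0.116 and 0.111, so 1 − 0.111/0.116 = 4%. The empirical SD of the estimates shows a smaller gap, 2 to 4% (0.1117 against 0.1143, 0.1161 against 0.1201, 0.114 against 0.119). With no true effect, the SE gap in the first simulation was 2 to 3%.

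**Dependence on the observed effect.** On average the rule picked 0.9 to 1.4 of the 8 covariates when an effect existed and 3.2 to 3.7 when there was none. With a true effect it left out the strongest predictor in 50 to 63% of runs.

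**Type I error.** Applied mechanically, about 0.034 in the first simulation and 0.047 in the second. Choosing the most favourable of the unadjusted, single-covariate and full models gave 0.061 to 0.081, against 0.038 to 0.050 for the unadjusted model.

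**Limit on adjusting rare outcomes.** If obesity at age 3 is about 2% (the Background gives 1.8% and 2.2% for ages 2 to 17), a two-arm comparison has about 2 × 417 × 0.02 ≈ 17 cases. At the Background's 13.3% and 14.9% for overweight, it has about 2 × 417 × 0.141 ≈ 118.

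**The case against.** The strongest defence is that little is left open. The candidate list is fixed, baseline values always enter, and an exact criterion is something an article may leave to a fuller plan. The 10% rule in the simulation is an assumption, as are R² and the covariate ICCs. This limits the size of the point but does not remove it. The article does not merely omit a criterion; it states that membership depends on the data. The unconditional baseline values also help little for the behaviours, because the inclusion questionnaire is a short set of background items completed when the child is a few weeks old.

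A reader might infer more than the document supports:

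- **That the rule inflates false positives.** Mechanically applied, it did not. Inflation appeared only when the best-looking model was picked, which the article does not propose.
- **That analysts choose the model unblinded.** The article does not say whether they are blinded.
- **That recruitment makes the arms unequal.** Families are approached by the team's nurse, with 50% consent expected, and the natural inference is that teams had already been allocated. Systematic imbalance is therefore possible, but it is not shown, and no simulation included it. It would also give screening some rationale, since imbalanced predictors tend to be retained. A fixed set would cover that case too, for the variables it contains.
- **That sex and age are ignored altogether.** The overweight and obesity cut-offs already allow for both. The gap is in continuous BMI, where it costs precision and is not in itself a source of bias under random allocation.

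It is also fair to object that one full set for every outcome would be wrong. With about 17 obesity cases it would overfit, and in logistic models adjustment changes the odds ratio being estimated and need not shrink its standard error. The remedy must differ by outcome.

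**Conclusion.** The point stands in a limited form. The article states a result-dependent covariate rule for its primary analyses, and nothing else in it fixes the adjusted model. The consequences are room for analyst discretion, models that may differ by outcome and arm, and a modest loss of precision: on model-based standard errors, about 4 to 6% in favour of a fixed set, with power about 0.68 against 0.64 at a true effect of 0.29 SD.

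These sizes apply to continuous outcomes. They rest on an assumed R² of about 0.17 and an assumed 10% change-in-estimate criterion, and they shrink towards zero with R². The finding about the wording of the rule depends on neither assumption. The change should be made, but the point does not invalidate the trial's conclusions.

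**What to change.** Replace the screening rule in Measurements, and the matching condition in Data analyses, with a covariate set named for each primary outcome before outcome data are analysed. Include it whatever the observed change in the estimate.

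- **Continuous outcomes:** keep the baseline values already planned; add birth weight, pregnancy duration, parental education, ethnic background, parental age and child sex. Include parental BMI and SF-12 only if measured at inclusion. Their timing is not stated, and the later questionnaires come after BBOFT+ has begun.
- **Continuous BMI:** also add exact age at measurement, or analyse BMI standardised for age and sex.
- **Overweight:** a short pre-specified set.
- **Obesity:** a minimal pre-specified set, stating that the odds ratio is conditional on it.
- **All outcomes:** report the unadjusted multilevel model as a sensitivity analysis.

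The cost is mainly wording, a few degrees of freedom in the continuous models, and a stated method for missing covariates. The listed variables are already planned for collection. The article does not say that exact age at measurement will be extracted, so its availability in the YHC files needs confirming.
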